### Participants

All participants are referred outpatients at one of four locations of Dimence, a specialised mental health care institution in the northeast of the Netherlands. Most patients are referred by their GP and have, after a short screening, been assigned to one of the departments that specialises in treating adults (between 18 and 65 years old) suffering from anxiety and mood disorders. The participants are recruited from the group that meets the criteria for single or recurrent, moderate or severe episodes of unipolar major depression (Diagnostic and Statistical Manual of Mental Disorders, fourth edition, (DSM-IV [55], 296.22, 296.23, 296.32, 296.33) as classified as the primary diagnosis by the MINI international neuropsychiatric interview [56, 57]. During the study, DSM-5 [55] has been introduced in the Netherlands. Patients diagnosed with the condition that was previously classified as dysthymia and patients with depressive symptoms that persist for less than 2 months after the death of a loved one are therefore not included in the study, despite the fact that, according to DSM-5, they would meet the criteria for a depressive episode.

Patients can be included only if no psychotherapeutic treatment in specialised mental health care has been provided in the previous year. Exclusion criteria are: insufficient mastery of the Dutch language, in so far that this means the patient is unable to complete the necessary research questionnaires; psychotic symptoms; substance dependency (with the exception of nicotine dependency); not being able to commit to treatment requirements (such as following treatment sessions) and severe risk of suicide requiring immediate intervention. Patients taking antidepressants are included only after taking the same dose of medication for at least 6 weeks. If these patients that are using medication are willing to participate, they are told that the dosage and the medication should not be changed during the course of the study. Changes in medication are allowed only when strictly necessary, for example because of hazardous side-effects. The use of medication is monitored during the course of the study.

### Procedures

Psychologists, psychiatrists and nurses taking part in the intake assessment are asked to inform patients who meet the inclusion criteria about the nature of the study. Patient leaflets about the study are provided and, if necessary, a member of the research team is available to answer any questions. If the patient wishes to participate and does not meet the exclusion criteria, he or she is asked to sign an informed consent form in the days or weeks after the intake procedure. For the purposes of stratified randomisation, the person performing the initial intake assessment provides a member of the research team with information about the duration of the depressive episode (longer or shorter than 2 years). After the completion of the baseline measurement, patients are randomly assigned to one of two conditions (SPSP or CBT). For an overview of the questionnaires included during baseline and the treatment phases, see Table 1. All questionnaires are completed on an online platform. Therapists and researchers are blind to all outcomes except non-response (yes or no) after phase 1 of treatment. After phase 1 of treatment and approximately 16 sessions planned over a period of 8 weeks of treatment, the researcher is informed whether the patient has responded to treatment (yes or no). Response is defined as an improvement of at least 50% of the post-treatment IDS-SR score by comparison with the baseline assessment. Patients who do not respond to treatment are randomly assigned to one of three different treatment conditions for the second phase, as described above.

### Randomisation

We use two potential moderators of outcome: severity (IDS-SR score < 39 or ≥ 39) and duration of depression (longer or shorter than 2 years) as stratification variables. Randomisation takes place using a system with closed envelopes in which the researcher is kept blinded to treatment allocation until the completion of the study phase and the patient is blind to the research condition until the start of the therapy. The therapist is given the information about the type of treatment to be administered shortly before the start of therapy.

Randomisation lists with an 1:1 allocation ratio were drawn up prior to the start of the inclusion of patients using an online tool [58]. Random block sizes are used. Block randomisation for phase two follows the same procedure as phase one, with an allocation ratio of 1:1:1. Patients receive a unique randomisation code that is linked to a unique patient number in the data file. The coding key is known to only one independent person. That person manages the data file that will be used for statistical analysis.

### Interventions

#### Short-term psychoanalytic supportive psychotherapy

Short-term Psychoanalytic Supportive Psychotherapy (SPSP) was developed by de Jonghe [16, 17]. SPSP is characterised by an open dialogue that allows the therapist to be as responsive as possible to relevant issues brought up by the patient. The therapy is based on a relational perspective relating to six psychoanalytic sub-theories: drift theory; egopsychology; object relationship theory; self-psychology; attachment theory and primary-love theory. The focus of the treatment is primarily on the affective, and if necessary behavioural, aspects of the client’s functioning in current relationships. It is assumed that past relational experiences continue to affect adult relationships and are related to the onset of depressive reactions. SPSP is a more supportive variant of short-term psychoanalytic psychotherapy, which means a secure helping alliance is considered to be a prerequisite. Expressive interventions to enhance insight into actual relational patterns or earlier experiences are always embedded in a supportive context. The most important therapeutic technique is adequate psychoanalytic support [17, 59]. This is present when developmental needs that are not adequately met during life are (in part) experienced within the therapeutic relationship. Adequate psychoanalytic support is present when there is a supportive attitude that is not only intended by the therapist but also experienced as such by the patient and promotes personal growth.

In order to enhance progress and help to find a focus, the SPSP sessions can be structured on the lines of eight different levels of discourse [17]. Levels one, two and three focus in succession on the patient’s physical and psychological symptoms and complaints, the influence of life circumstances on the depressive symptoms, and the influence of external interpersonal relationships on the depressive symptoms. At the fourth and fifth level the focus shifts to one or more relational patterns in the patient’s life and the patient’s attitude in life, respectively. The sixth level works on how past relationships persist in the patient’s current life, and the seventh level addresses the intrapersonal relationship the patient maintains with himself or herself as a consequence of identification with these past relationships. At the eighth level the focus shifts to how the problems discussed at levels four to seven manifest themselves in the relationship with the therapist. The levels of discourse can vary considerably during the course of treatment. Short Psychodynamic Supportive Psychotherapy has been described by de Jonghe in a treatment protocol [60] which is used in the current study.

#### Cognitive behavioural therapy

Cognitive Behavioural Therapy (CBT) was developed by Beck [61] and it is based on the cognitive theory. The cognitive component of CBT aims to locate and correct negative automatic thoughts and logical errors, and to change ‘schemata’ and therefore alleviate the depressive symptoms. In addition to this cognitive element, CBT has a behavioural component that is based on the notion that depression is partly caused or maintained by a lack of pleasant or satisfactory activities in line with the theory of Lewinsohn [62]. In CBT, patients are therefore encouraged to identify activities that affect their mood positively and engage in them more often. CBT in general is further characterised by a limited time span and a structured approach. The focus of therapy is mostly on the present. Homework assignments are an important part of the treatment and patients use a workbook to register assignments. CBT is delivered in accordance with an existing protocol [63] and it is based on the principles for treating depression described by Beck [61] and the behavioural model described by Lewinsohn [64].

### Assessments

#### Primary outcome measure

##### Depression: inventory of depressive symptomatology

The self-report version of the Inventory of Depressive Symptomatology (IDS-SR; Dutch translation Altrecht GGZ [52, 65]) consists of 30 items that are scored on a four-point scale. The total score ranges from 0 to 84. The IDS-SR has acceptable psychometric properties and it is a treatment-sensitive measure in depressed outpatients [65–67].

#### Secondary outcome measures

##### Functional impairment: Sheehan disability scale

The Sheehan Disability Scale (SDS [68], Dutch translation) measures functional impairments that are caused by symptoms. Three ten-point scales measure to what extent symptoms impair function in three domains. The sum score, which ranges from 0 (unimpaired) to 30 (highly impaired), gives an overall impression of the level of impairment experienced by the patient. Leon et al. [69] report high internal consistency. Their analyses also provide empirical support for construct validity.

##### Positive mental health: mental health continuum-short form

The Mental Health Continuum-Short Form (MHC-SF, Dutch translation [70]) comprises 14 items. The occurrence of various types of feelings of well-being in the last month are rated on a six-point Likert scale. The total score on the scale can range from 0 to 70 points. Higher scores indicate a higher level of well-being. High internal and convergent validity and moderate test-retest reliability have been reported [70].

#### Potential predictors

##### Demographic variables

Patients complete a short questionnaire regarding a number of demographic variables regarding gender, age, cultural background, marital status, education, employment status and income.

##### Traumatic life-events (including recent): list of threatening experiences

The List of Threatening Experiences [71, 72] (Dutch translation) consists of descriptions of 21 life events and an assessment of occurrence (yes or no) before and after the sixteenth year of life and during the past twelve months. The checklist has shown to have high test-retest reliability and good agreement with informant information [71, 73].

##### Life events (lifetime): checklist life events for DSM-5

The Checklist Life Events for DSM-5 (LEC-5) [74], Dutch translation [75]) is a self-report measure that assesses lifetime exposure to 16 potentially traumatic events. Different levels of exposure (on a six-point nominal scale) can be indicated by the respondent. Psychometrics are not available for the LEC-5 but the similar LEC for DSM-IV has been shown to have adequate psychometric properties [76]. Given the minimal revisions by comparison with the original version of the LEC, few psychometric differences with the latest version are expected.

##### Symptoms: brief symptom inventory

The Brief Symptom Inventory (BSI [77], Dutch translation [78]) is a brief psychological self-report symptom scale with good psychometric properties. It consists of 53 items that are scored on a five-point scale. The BSI shows the extent to which the person has suffered from psychological and / or physical symptoms during the past period. The BSI has nine subscales: Somatisation (SOM), Obsessive-Compulsive (O-C), Interpersonal Sensitivity (I-S), Depression (DEP), Anxiety (ANX), Hostility (HOS), Phobic Anxiety (PHOB), Paranoid Ideation (PAR), and Psychoticism (PSY). The measure also provides a score for the total number of complaints, total symptoms and symptom severity.

##### Agoraphobia: the agoraphobia scale

The Agoraphobia Scale (AGO, [79]) consists of 20 items concerning agoraphobic situations. These are rated for anxiety/discomfort (0–4) and for avoidance (0–2). The AGO is a valid and reliable instrument [79].

##### Self-esteem: Rosenberg self-esteem scale

The Rosenberg Self-Esteem Scale (RSES [80]; Dutch translation [81]) is designed to measure self-esteem. The RSES consists of 10 items that are scored on a 4-point scale ranging from “completely agree” to “completely disagree”. The RSES has good psychometric properties [81, 82].

##### Rumination: rumination response scale

The Rumination Response Scale (RRS [83]; Dutch translation [84]) is designed to measure ruminative thoughts and behaviours in patients with MDD. It consists of 22 items that are scored on a four-point scale ranging from “almost never” to “always”. The RRS has good psychometric properties [83].

##### Defence mechanisms: defense style questionnaire

The Defense Style Questionnaire (DSQ [85], Dutch translation [86]) is a self-report inventory that measures specific defence mechanisms. The DSQ consists of forty items in a nine-point Likert format that derive scores for twenty defence mechanisms, two items for each. These mechanisms are organised as four sub-factors (immature, mature, image-distorting and neurotic). The DSQ has proven to be a valid and reliable instrument.

##### Personality organisation: inventory of personality organisation

The Inventory of Personality Organisation (IPO [87], Dutch translation [88]) is a self-report instrument intended to measure a patient’s level of personality organisation. The IPO is a 57-item self-report questionnaire with three scales, each relevant to a different dimension of Kernberg’s personality organisation model. All items are rated on a five-point Likert-scale format ranging from 1 (never true) to 5 (always true). Adequate internal consistency and good test-retest reliability have been reported [89].

#### Alliance, therapist characteristics and allegiance

##### Working Alliance: working Alliance Inventory-12

The client version of the Working Alliance Inventory (WAI [90], Dutch Translation [91]) measures the quality of the therapeutic relationship as perceived by the patient. The WAI-12 is a shortened version for measuring the therapeutic relationship and it consists of twelve items, each item being judged on a five-point scale (1 = rare or never, 5 = always). In 2009, the WAI-12 was validated for the Flemish population and the three-factor structure of the WAI-12 was confirmed [92].

##### Therapist characteristics: Counsellor rating form-short version (CRF-S)

The CRF-S [40] measures the reliability and expertise of the therapist as perceived by the patient. The reliability of the condensed version (CRF-S [41]) appeared to be comparable to the full version. The shortened CRF consists of 12 items, with all items scored on a seven-point rating scale ranging from “not very” to “very”. Due to the absence of an existing Dutch translation, the CRF-S was translated into Dutch for the current study. The translation procedures of Beaton et al. [93] were followed for this purpose.

##### Allegiance

Allegiance is measured using a questionnaire that is filled in by the therapists. It contains 14 questions, that are rated on a 5-point Likert scale, for example about the number of years of experience with the particular method, the amount of training followed in the respective treatment method, the therapists willingness to further develop oneself as a CBT or SPSP therapist through training or supervision, if the therapist visits specific congresses or meetings pertaining to the particular treatment method and to what extent he or she has confidence in the effectiveness of the particular treatment. The higher the score, the higher the indicated degree of allegiance. Also a question with regard to the general allegiance of a practitioner is included. The questionnaire is based on recommendations by Leykin and DeRubeis [51], which are partly based on research by Luborsky et al. [48, 94].

#### Treatment integrity

About 40 therapists are expected to take part in the study. The exact number will depend on various circumstances such as the time it takes to include all patients and the therapists turnover rate in the locations. The minimum requirement to participate as a therapist in the study is a master’s degree in medicine or psychology. Therapists cannot start treating patients included in the study until they have received a three-day course in SPSP and a three-day course in CBT for depression that are given by qualified and experienced experts. Audio recordings are made of every treatment session to ensure and measure treatment integrity. Recordings are discussed in the presence of peers during supervision that is given by trained supervisors every 2 weeks. Training and supervision sessions for SPSP are therefore based on the Handbook of Short-Term Psychoanalytic Supportive Psychotherapy [60]. CBT training is also based on an existing Dutch CBT protocol [63]. There is no scale for measuring treatment integrity for SPSP and within this study we will develop and test an instrument that measures the most important method specific elements of SPSP, namely adequate psychoanalytic support and the different levels of discourse. Adherence in CBT was measured with the Cognitive Therapy and Adherence Scale (CTACS) [95]. The CTACS measures competence as well as adherence for CBT in general. It has been extensively studied in patients suffering from cocaine dependence but was designed and is appropriate for measuring both competence and adherence for all types of CBT. It has good internal reliability and acceptable interrater reliability [95]. The criterion validity of the scale is high [96, 97]. In the current study, the applicability of the CTACS will be studied specifically for depressed patients.

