### Power and sample size calculation

To calculate the required sample size for the first phase of the study we used the original dataset provided by the authors of a similar study which was conducted in a similar setting and population [19]. We expected this to be the best data available to make an accurate estimate of the standard deviation of the primary outcome needed to calculate the sample size.

The primary outcome measure of the current study is the severity of depressive symptoms as measured by the IDS-SR [52]. To test whether SPSP is in fact (as hypothesised) not inferior to CBT, a treatment that has already proven to be effective for treating MDD, we used the same non-inferiority margin (the maximum allowed difference in the mean outcome scores between the treatment groups to conclude that SPSP is indeed non-inferior to CBT) for continuous measures as Driessen et al. [19, 53] Accordingly, we adopted a non-inferiority margin of five points on the mean score on the IDS-SR immediately after treatment. This margin of a five-point difference between SPSP and CBT corresponds to a Cohen’s d of .30, which we assume to be a clinically acceptable difference. Power analysis for continuous outcomes [54] indicated that, to prove that SPSP is not inferior to CBT, 268 patients in total are needed for the first part of the study to provide 80% power in order to demonstrate that the lower limit of the one-sided 95% confidence interval (CI) will be above the non-inferiority limit of − 5 for the IDS-SR (1-β = 80%, SD = 16.42). Given the observed dropout rate of around 15% for the first 100 included patients, the aim is to include 308 patients for the performance of the per-protocol analysis.

Assuming that approximately 52% of the patients will be classified as non-responder after the first phase of study [4], we estimate that around 139 patients can be randomized across the three groups (1. same therapist, same treatment, 2. a switch of therapist only, 3. a switch of therapist and treatment) in the second phase of the study. According to a sensitivity analysis, by means of an analysis of covariance (ANCOVA), this suggests that we can significantly (α = .05) demonstrate a medium to large effect size (f = 0.35) with 80% power between the three groups in the second phase of the study.

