### Statistical analysis

#### Establishing non-inferiority

The study compares the effectiveness of two forms of treatment (SPSP and CBT). The primary dependent variable is the average post-treatment score for the two groups on the IDS-SR. An ANCOVA with treatment type received as a fixed effect and baseline depression scores measured on the IDS-SR as a covariate will be performed to calculate the mean and 95% CI of the difference between the groups at the final time point on the IDS-SR. This analysis forms the basis for demonstrating that SPSP reduces depressive symptoms at least as effectively as CBT. If the lower limit of the 95% CI is above the non-inferiority limit of − 5 on the IDS-SR, it will be assumed that SPSP is not inferior to CBT. Non-inferiority analysis will be performed on the basis of both per protocol and intention-to-treat analysis.

Additional multilevel repeated measures will be used to further analyse changes in depressive symptoms and the other secondary outcome measures (functional impairment and positive mental health) and to examine possible differences between both treatment groups over time. If there are significant differences between groups in medication use or other potentially confounding variables, these variables will be included as covariates.

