#### Moderator and mediator analysis

Most moderator and mediation analysis regarding allegiance and adherence will be performed with regression-based methods [98]. Additionally, cross-lagged panel analysis will be used to investigate the directionality and reciprocity of the relations between working alliance (WAI) and symptoms (IDS-SR) over time [99, 100]. We will also study whether a cut-off score for the working alliance can be determined that is predictive of a significantly lower treatment result by means of an receiver operating characteristic analysis. In line with Zilcha-Mano [101] the relative speed of change in the quality of the working alliance for each patient will also be explored in an additional analysis as a possible factor that influences outcome since, in her theory, some patients are better equipped to benefit from the therapeutic relationship.

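### The primary ANCOVA and the sample size treat patients as independent although about 40 therapists deliver the treatments, so the non-inferiority interval may not have its nominal coverage

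*Protocol article*

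**What the plan says.** - **Therapists.** Under Treatment integrity: "About 40 therapists are expected to take part in the study". The same section says "Therapists cannot start treating patients included in the study until they have received a three-day course in SPSP and a three-day course in CBT". It does not say whether each therapist then treats study patients in both arms.
- **Primary model.** Under Establishing non-inferiority: "An ANCOVA with treatment type received as a fixed effect and baseline depression scores measured on the IDS-SR as a covariate". Medication use and other potential confounders may enter if the groups differ significantly on them. No therapist term is named.
- **Sample size.** Under Power and sample size calculation, "we adopted a non-inferiority margin of five points on the mean score on the IDS-SR immediately after treatment". The other inputs are a one-sided 95% interval and "1-β = 80%, SD = 16.42", giving 268 evaluable patients. There is no intraclass correlation or design effect.
- **Other models.** The further phase-one analyses and the phase-two analysis are described as multilevel repeated measures, without naming the levels. For the therapist measures: "Most moderator and mediation analysis regarding allegiance and adherence will be performed with regression-based methods".
- **Allegiance.** "Allegiance is measured using a questionnaire that is filled in by the therapists".

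**The concern.** Patients treated by the same therapist may have correlated outcomes. This trial has particular reason to allow for that. Phase two changes the therapist as an experimental factor. The Background raises the possibility that a new therapist alone could help, and that a therapist may deliver better a method he or she believes in. The Discussion expects most therapists to have more experience with CBT.

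The primary model is spelled out, so this is not a detail left open for an analysis plan. As written, its standard error is that of independent patients. If the true standard error is larger, the interval is too narrow and non-inferiority is claimed too easily. If it is smaller, the interval is too wide and power is lost. The sample size was set at 80% with no reserve.

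**Working it through.** **Inputs from the article.** Margin 5; SD 16.42; one-sided 5%; power 80%; 268 evaluable patients (134 per arm); about 40 therapists.

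**Assumptions.** Equal caseloads, m = 268/40 = 6.7. No intraclass correlation is given, so therapist shares of the variance totalling 5% are used. The baseline covariate is taken to remove no variance.

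**Step 1: reproduce the stated figure.** With independent patients, SE = 16.42 × √(2/134) = 2.006. Power = Φ(5/2.006 − 1.645) = Φ(0.848) = 80.2%. The usual normal-approximation formula returns 134 per arm, 268 in total. The stated number therefore contains no allowance for therapists.

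**Step 2: design effect (DE).** Let a be the share due to a therapist main effect and b the share due to therapist-by-method variation.
- Therapists crossed with arm, balanced: DE = (1 − a − b) + (m/2) × b = (1 − a − b) + 3.35b.
- Therapists each delivering one method, total share ρ: DE = 1 + (m − 1)ρ = 1 + 5.7ρ.
- Actual one-sided error of the plain analysis: 1 − Φ(1.645/√DE).
- Power at 268 when the interval has the correct width: Φ(5/(2.006√DE) − 1.645).

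| Structure | a | b | DE | Error | Power |
|---|---|---|---|---|---|
| Crossed | 5% | 0 | 0.95 | 4.6% | 82% |
| Crossed | 2.5% | 2.5% | 1.03 | 5.3% | 79% |
| Crossed | 0 | 5% | 1.12 | 6.0% | 76% |
| One method per therapist | ρ = 5% | – | 1.285 | 7.3% | 71% |

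Third row in full: 0.95 + 3.35 × 0.05 = 1.1175, √1.1175 = 1.057, error 1 − Φ(1.645/1.057) = 6.0%, power Φ(2.492/1.057 − 1.645) = 76%.

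**Step 3: unequal caseloads.** A simulation of the unadjusted comparison (268 patients, 40 therapists, patients allotted to therapists at random, 20,000 runs, Monte Carlo standard error about 0.15 percentage points) gave errors of 5.3%, 6.0% and 6.3% for the three crossed rows and 7.9% for the last row. The small gain in the first row thus depends on each therapist's patients being evenly split between arms. Without that balance, the error is close to nominal.

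**Step 4: allegiance, only if its regression has no therapist level.** For a predictor that is constant within therapist, DE = 1 + 5.7 × ICC. At ICC 0.05 and 0.10 this is 1.285 and 1.57, and the two-sided error 2(1 − Φ(1.96/√DE)) is 8.4% and 11.8%. If scores are specific to method, and a therapist's two sets of patients are taken as independent, clusters halve to 3.35 patients. DE is then 1.12 and 1.235, and the errors are 6.4% and 7.8%.

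**The case against.** A reader might infer that the primary interval is simply wrong. The documents do not support that. Training every therapist in both methods points to crossing, and then a main effect and a therapist-by-method effect push in opposite directions. With 5% main and 2.5% interaction, DE is 0.925 + 3.35 × 0.025 = 1.01 and the error is 5.1%. The last row of the table needs a structure that the article nowhere states. This objection stands and sets the limit of the point.

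The expected CBT experience is also weak evidence of therapist-by-method variation, since a lead shared by most therapists mainly shifts the mean difference between arms. The remarks on therapist confidence are tentative. Both stand: such variation is plausible here but not asserted.

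The baseline covariate may restore the power. If 16.42 is an unadjusted SD and the baseline–outcome correlation is 0.3 or 0.4 (assumed), DE 1.12 leaves about 80% or 82%. This stands for power; it does not correct the coverage.

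The analysis section gives a 95% interval without saying whether it is one-sided. If it is two-sided, the nominal one-sided error is 2.5%, and DE 1.12 raises it to 3.2%. The relative inflation is of the same order.

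The Discussion offers adjustment for experience, allegiance and integrity. That may absorb some therapist variance, but it leaves the remainder unmodelled.

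A reader might also infer that the allegiance and phase-two models ignore therapists. Neither is established: regression-based methods can include a therapist level, the phase-two model is multilevel with unnamed levels, and a condensed article may leave both to the full plan.

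**Conclusion.** The point holds in a limited form. The primary model and the sample size take patients as independent in a trial with about 40 therapists and an explicit interest in therapist effects. Coverage of the non-inferiority interval therefore depends on variance components that are neither modelled nor stated. With therapists crossed with arm and 5% of the variance at therapist level, the one-sided error lies between about 4.6% and 6.0% under balance (up to 6.3% with random caseloads) and the power between 82% and 76%. About 7.3% and 71% would arise only if therapists in practice delivered one method.

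These figures rest on the assumed shares, a nominal one-sided 5% and no gain from the baseline covariate. The effect on the primary contrast is modest and its direction unknown. For allegiance and phase two the point is conditional: it matters only if those models omit the therapist.

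**What to change.** - Add random effects for therapist and therapist-by-treatment to the primary model, or at the least prespecify that model as a sensitivity analysis.
- State whether therapists treat patients in both arms.
- Restate the power under an assumed therapist variance share, for example 5%, split between main effect and interaction.
- In phase two, if no therapist level is planned, include one for the therapist treating in that phase. In the allegiance models, likewise include a therapist level if there is none, because allegiance is measured on the therapist.

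The cost is analysis wording, best settled before unblinding. Recruitment and treatment are unaffected. It does require each patient's treating therapist to be in the analysis file. The interval may widen slightly and the stated power may fall by a few points.
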